### Power and sample size

Based on the feasibility study’s data,^23^ using our primary outcome of the SPADI at 12-month follow-up, to show a worthwhile difference of eight points with 90% power and 5% level of significance with an SD of 21.1,^44^ we need data on 292 participants. Allowing for 25% loss to follow-up, a total of 390 participants (195 in each group) will be required with an allocation ratio 1:1. We will require a total of 17 physiotherapists, each with an average of 12 patients to deliver the intervention. The loss to follow-up over 12 months has been modelled on 25% based on the previous literature^45^ and a greater proportion of participants in this trial being assessed at 12 month compared with our feasibility study.^23^ We will be striving to achieve a follow-up rate of >75%.

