### Internal pilot

The first 6 months of randomisation will be an internal pilot, with a green target of 40 randomised. The pilot will take place in a minimum of four hospitals, selected to offer diversity across the population while also representative of centres/physiotherapists that will take part in the main trial. The progression criteria are presented in table 1.

**Table 1 T1:** Stop–go criteria for internal pilot

Red	Amber	Green
N participants recruited	≤26 (<66%)	27–39 (66%–99%)	≥40 (100%)
Recruitment rate/site/month	< 1 participant	1–2 participants	3 participants
Number of sites opened	1 site	2–3 sites	4 sites
Intervention session attendance*†	≤27 (<70%)	28–39 (≥70%–<99%)	≥40 (100%)
Loss to follow-up†	≥10 (>25%)	1–9 (1%–25%)	0 (0%)

* Minimum one assessment and three follow-up appointments (four sessions in total) or if patient–physiotherapist goals met and agreed discharge made prior to this session number.

† Analysed at 12-month follow-up of the cohort randomised in first 6 months to obtain sufficient data.

If the internal pilot meets amber criteria, we will consult the funder, inform the TSC, review processes, look to open additional sites or amend trial processes and review again in 6 months. If the red criteria are met across all indicators, we will discuss stopping the trial with the TSC and funder.

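### Table 1's loss-to-follow-up row gives two classes to the loss the trial is planned on: 10 of 40 is red by count and amber by percentage

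*Protocol article*

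**What the plan says.** The Internal pilot section states: "The first 6 months of randomisation will be an internal pilot, with a green target of 40 randomised". Table 1 then sets red, amber and green bands for five indicators, most of them as a count with a percentage in brackets. The loss row reads "Loss to follow-up† ≥10 (>25%) 1–9 (1%–25%) 0 (0", so green is zero losses. A footnote places the assessment of this row at 12-month follow-up of the participants randomised in the first six months.

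The text below the table attaches actions to the bands. Amber leads to consultation with the funder, notice to the Trial Steering Committee (TSC), changes to sites or processes, and a further review after six months. Stopping is discussed only when every indicator is red.

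Power and sample size uses the same quantity, loss at 12 months, as a planning value: "Allowing for 25% loss to follow-up, a total of 390 participants (195 in each group) will be required". It gives the basis as follows: "The loss to follow-up over 12 months has been modelled on 25% based on the previous literature". The section also says that the team will aim to retain more than 75%.

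**The concern.** A progression threshold should give one class to each result. Here the count and the bracketed percentage are two different rules, and they part at the value a reader would check first, the 25% that the sample size assumes. Nothing printed says which of the two governs.

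At stake is how the pilot's retention result is reported to the TSC and funder. If the choice between count and percentage is left until the 12-month losses are known, it becomes a post hoc choice. The counts are also fixed numbers, while the number randomised in six months is not known in advance, so the disagreement need not be confined to a cohort of exactly 40.

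**Working it through.** **Inputs.** From Power and sample size: difference 8 points, SD 21.1, 90% power, 5% significance (two-sided assumed), 292 evaluable, 25% loss, 390 in total. From Internal pilot and Table 1: target 40 randomised; loss red at 10 or more (labelled above 25%), amber at 1 to 9 (labelled 1% to 25%), green at 0; recruitment red at 26 or fewer, amber at 27 to 39, green at 40 or more.

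**The plan's own figures.** Per group, n = 2 × (1.960 + 1.282)² × 21.1² / 8² ≈ 146.2, or about 292 in total (294 if each group is rounded up). Then 292 / 0.75 = 389.3, rounded up to 390. The sample size reproduces and is not in question.

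**The row at 40 randomised.**
- 9 / 40 = 22.5%: amber by both labels.
- 10 / 40 = 25.0%: red by count; amber by percentage, because 25% is not above 25%.
- 11 / 40 = 27.5%: red by both labels.

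**Size at the planning value.** Let X be the number lost, binomial with n = 40 and p = 0.25 (losses assumed independent).
- Red by count: P(X ≥ 10) = 0.560.
- Red by percentage: P(X ≥ 11) = 0.416.
- The labels disagree: P(X = 10) = 0.560 − 0.416 = 0.144.

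**Other cohort sizes.** The labels disagree when 10 or more losses is no more than 25% of the cohort, or when 9 or fewer losses is more than 25%.

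| Randomised | Losses where labels differ | Percentage lost | By count | By percentage |
|---|---|---|---|---|
| 26 | 7 to 9 | 26.9 to 34.6 | amber | red |
| 27 | 7 to 9 | 25.9 to 33.3 | amber | red |
| 35 | 9 | 25.7 | amber | red |
| 36 to 39 | none | 9 lost is at most 25.0; 10 lost is at least 25.6 | same | same |
| 40 | 10 | 25.0 | red | amber |
| 50 | 10 to 12 | 20.0 to 24.0 | red | amber |

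Within the amber and green recruitment ranges, the labels agree for every number of losses only at 36 to 39 randomised. At 50 randomised and 25% true loss, P(X ≥ 10) = 0.836.

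**Link to the all-red condition.** With 40 randomised the recruitment row is green, so all-red is impossible and the 10-of-40 conflict cannot lead there. With 26 or fewer, recruitment is red, and 7 to 9 losses is red by percentage but amber by count. If the site and rate rows are red as well (one site, fewer than 1 participant per site per month), six months gives fewer than 1 × 1 × 6 = 6 participants. Ten losses cannot then occur, so the loss row cannot be red by count. By percentage it can: 2 / 5 = 40%.

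**Green.** P(X = 0) is 0.75⁴⁰ ≈ 0.00001 at 25% loss, 0.90⁴⁰ = 0.015 at 10% and 0.95⁴⁰ = 0.129 at 5%. Amber by count (1 to 9) then has probability 0.980 at 10% loss and 0.871 at 5%.

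**The case against.** The best defence is that this is a slip of one participant at one boundary. At 40 randomised only exactly 10 losses is affected. The row still separates 9 losses from 11, and the red/amber line sits at the planning allowance, where it belongs. The percentages are printed and could be applied to any cohort. The row is read at 12 months, so it cannot hold up progression at month six, and it does not touch the primary estimate, the error rates or the power. All of this stands and limits the weight of the point. It does not say which label governs, and the labels differ over a wider range of losses once the cohort is well away from 40.

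The stated aim of retaining more than 75% could be read as placing 25% loss in red. That would need red at 25% or more and amber below 25%, and the table prints neither.

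Three stronger readings are tempting and not supported.
- A reader might infer that a pilot performing as planned fails. By percentage the planned value is amber, which means review and continue, and a single red row does not trigger the stopping discussion.
- A reader might infer that the counts misclassify whenever the cohort is not 40. They do so only for some loss numbers: 5 of 50 is amber by both labels.
- A reader might infer that a zero-loss green contradicts the 25% allowance. An inflation allowance is not a target, and the attendance row also sets green at 100%. A strict green is a design choice.

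**Conclusion.** The row contradicts itself at the planning value. Ten of 40 is 25.0%, red by count and amber by percentage. At a true loss of 25% the chance of red is 56% or 42% depending on the label, with a 14% chance of landing on the ambiguous value. The labels also diverge for some loss numbers at cohorts of 35 or fewer and of 40 or more. In small cohorts, the label used can decide whether the all-red condition is met.

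This rests on three assumptions: a denominator of 40, which the table's 100% figures imply but the row does not state; independent losses; and, for the all-red calculation, that the site, rate and loss rows describe the same six-month cohort. The error lies in a stated progression threshold. It does not affect the sample size or the main analysis, and it does not make the pilot as a whole fail.

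**What to change.** Before the pilot's 12-month data are seen, define the row as a percentage of pilot participants randomised, and give counts for 40 as illustration only. Make the two agree in one of two ways:
- red above 25% (11 or more of 40), with amber up to and including 25% (up to 10); or
- red at 25% or more (10 or more of 40), with amber below 25% (up to 9).

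The second fits the stated aim of retaining more than 75%; the first keeps the printed percentages. The cost is a change to one row, agreed with the TSC and funder, with no new data.

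Separately, and only as a suggestion, the TSC and funder could reconsider the zero-loss green, since true loss of 5% to 10% would score amber about 87% to 98% of the time. The documents give no basis for a particular bound, so it is theirs to set. The price of relaxing it is that green becomes easier to reach.

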### Statistical analysis

A detailed statistical analysis plan (SAP) will be written inline with the Estimand framework^46^ and approved by the DMC prior to the primary analysis taking place. Data will be reported inline with the CONSORT guidelines.^47^ Descriptive statistics will be constructed for baseline and follow-up data. Graphical summaries will also be created to aid the interpretation of key results.

Primary outcome analyses will adopt the Estimand framework.^46^ The SPADI score will be analysed using the treatment policy strategy (ie, intention to treat). Treatment effects (with 95% CIs) will be estimated using mixed-effect linear regression models. Both unadjusted and adjusted (for stratification variables and important patient-level covariates) estimates of the treatment effect will be presented. Secondary outcomes will be analysed using a similar approach to the primary outcome as appropriate to data and its distribution. Secondary outcomes, which are categorical, will be analysed using mixed-effect logistic regression models. Intercurrent events (ICEs) and strategies for handling ICEs: postrandomisation events that may affect the interpretation of the primary outcome would include non-adherence (including discontinuation of treatment) (ICE1). The ICE1 will be analysed using the complier average causal effect analysis.

There are no formal interim analyses. Planned subgroup analyses will be conducted. Missing data will be scrutinised and where possible, the reason for missingness recorded. If appropriate, multiple imputation will be used. Any imputation methods used for scores and other derived variables will be carefully considered and justified. In the case of missing outcome data, we will compute sensitivity analyses using imputation techniques to examine the impact of missingness. Further details on the main and sensitivity analyses will be provided in the SAP.

### Database

All data will be entered and stored in a bespoke database management system developed by the programming team at WCTU. This is supported by a detailed data management plan (DMP) produced in accordance with WCTU SOPs to ensure the high-quality data collection throughout the duration of the trial.

### Health economic evaluation

For the base-case analysis, a parallel, within-trial, economic evaluation from the NHS and personal social services perspective will be conducted, with a broader societal perspective considered in a sensitivity analysis. A health economics analysis plan (HEAP) will be developed prior to data analysis. The methods will adhere to the National Institute for Health and Care Excellence (NICE) recommended standards for economic evaluation^48^ and the internationally recognised Consolidated Health Economics Evaluation Reporting Standards guidelines for reporting economic evaluations.^49^ The cost of the intervention groups will be estimated to reflect resource inputs associated with rehabilitation and broader healthcare use. A detailed microcosting exercise for the intervention will be undertaken, including costs of development, training and supporting of physiotherapists and delivering the physiotherapy sessions. We also plan to collect information on medication, resource use in primary and community care settings (eg, GP visits, community/district nurse, physiotherapy and other allied health professional visits and home services), outpatient services (eg, Accident and Emergency (A&E) visits, physiotherapy, radiology, diagnostic imaging service, surgical and medicine services), inpatient services (eg, critical care admission and admission in hospital wards), aids and adaptation used and personal and social services (eg, meals on wheels, home care worker contacts and social worker contacts), and any broader resource use. Unit costs will be estimated from both local and national sources and reflated to current prices where necessary and presented in £ sterling. HRQoL will be measured at baseline and all follow-up timepoints using the EQ-5D-5L measure. Responses will be used to generate quality-adjusted life years (QALYs) using the appropriate value set recommended by NICE at the time of the analysis.^48^

Descriptive statistics will summarise costs and QALYs by the intervention and comparator groups. The pattern of missing data will be examined and accounted for using suitable methods for multiple imputation. Within-trial analysis using bivariate regression of costs and QALYs for the base-case analysis, with imputation of missing data will inform deterministic and probabilistic assessment of incremental cost-effectiveness and results will be expressed as an incremental cost per QALY gained. Sensitivity analyses from a societal perspective will account for productivity losses and personal expenses incurred by participants due to their condition. To measure productivity losses, we will collect information on employment status (ie, whether retired, student and full- or part-time worker), employment details (eg, employment category and employment details), educational and professional qualifications and number of days off work due to illness. Probabilistic sensitivity analyses will be undertaken to explore parameter uncertainty. Results will be graphically displayed on a cost-effectiveness plane. Cost-effectiveness acceptability curves will show the probability of cost-effectiveness at a range of willingness-to-pay thresholds. If costs and outcomes do not converge within the 12 months, economic modelling will be undertaken to explore costs and benefits over an extended time horizon. If an economic model is needed, it will be populated using data from the trial, published literature and expert opinion. A 3.5% discount rate will be applied to both costs and QALYs beyond 12 months.

### Process evaluation

This process evaluation uses a mixed-methods approach to examine the implementation, fidelity, mechanisms of impact and contextual factors influencing the delivery and uptake of the GRRAND programme.

Quantitative data will include participant adherence rates, measured using the EARS^29^ at 6 weeks for all participants and during the physiotherapy discharge session for those in the intervention group. Fidelity will be assessed through structured session observations (n~12), informal discussions with staff accompanied by field notes and CRF checks monitoring variables, such as session number and duration. Pre- and post-training questionnaires completed by physiotherapists will assess changes in confidence and knowledge. Descriptive statistics will be used to analyse quantitative data.

Qualitative data will be collected through semistructured interviews or focus groups with approximately 12 participants from the intervention group, 12 from the control group and 24 physiotherapists. Interviews will explore the acceptability of the intervention and address key themes, including contextual influences (eg, how local circumstances shaped experiences), mechanisms of change (eg, how the intervention supported recovery) and perceived outcomes. Physiotherapists will additionally reflect on implementation challenges and enablers, including local organisational conditions and culture. Purposeful sampling will be used, aiming for diversity across clinical and demographic variables, such as setting (urban vs remote), cancer stage, presence or absence of accessory nerve sacrifice, age, gender and exercise adherence levels. Sampling will also consider whether patients accessed external physiotherapy services. Qualitative data will be analysed using an interpretive descriptive approach.

Integration of qualitative and quantitative findings will be conducted through triangulation, using a convergence matrix to synthesise insights. This will enable the identification of patterns linking process metrics with outcomes and support understanding of what works, for whom and under what circumstances. A logic model outlining the theoretical underpinnings and intended mechanisms of the GRRAND programme is provided (figure 2) to guide and support the process evaluation.

**Figure 2 F2:**
[figure not shown]
GRRAND programme logic model. GRRAND, getting recovery right after neck dissection; HRQoL, health-related quality of life.

## Ethics and dissemination

The trial was approved by the London-Brent REC (ref: 24/LO/0722). The GRRAND trial will adhere to the Declaration of Helsinki^50^ and good clinical practice principles, complying with all relevant WCTU SOPs. Participants will provide informed consent before agreeing to take part. An independent DMC and TSC will provide oversight from set up to the end of the trial. Both committees will comprise independent members as per National Institute for Health and Care Research (NIHR) and WCTU SOPs. Members will sign separate committee charters. The trial sponsor will implement DMPs. Protocol amendments will be disseminated to sites by the trial coordinating team.

## Data sharing

Deidentified data underlying the trial results will be available for non-commercial use, up to 1 year after publication of the trial findings, or from metadata stored in a university repository up to 5 years without investigator support. To access trial data, third parties must complete a data-sharing agreement with the sponsor, have an ethically approved protocol in place for use of the data and agree the approved protocol with the GRRAND TMG and WCTU Data-Sharing Committee. Data may be used for commercial purposes, according to the conditions above, but will need specific agreements in place prior to access being agreed and may include a licence fee. Analyses may include individual patient data meta-analyses or other purposes as agreed with the GRRAND TMG.

Available data will include (but is not exclusive to) deidentified individual participant data, the trial protocol, SAP, HEAP, master copy of the informed consent sheets and scripts or files used to conduct trial analyses.

## Trial registration and study timelines

The trial is registered with the nternational Standard Randomized Controlled Trial Number (ISRCTN) register (ISRCTN13855775). The current version of the protocol is V.2.0, approved on 13 March 2025. The planned dates of the study are from February 2025 to December 2027.

## Dissemination and publication

Results will be shared with trial collaborators, while the main results paper is drafted by the trial team and agreed by the TSC prior to submission to a major peer-reviewed journal. Summary briefing papers, press releases and social media posts (specifically aimed at UK audiences) will be prepared for the wider community with specific input from our PPI team. These outputs will allow for the results to be disseminated across the orthopaedic and rehabilitation communities, the wider medical community, policymakers and patients and society at large in the UK, and globally. Dissemination to trial participants will follow current Health Research Authority guidelines, with summaries available on the GRRAND website and social media as appropriate.

## Data Availability

Data are available on reasonable request.
